## Abstract

**Introduction:**

Virtual reality (VR) has increasingly found applications beyond leisure and video games, extending into the field of medicine. Recent studies indicate that VR can effectively reduce anxiety and pain in pediatric patients undergoing uncomfortable medical procedures, such as burn wound care. Yet, VR use in the operating room is still rare, despite a growing trend toward regional anesthesia without general anesthesia; physicians still frequently rely on pharmacological sedation to manage procedural anxiety. By leveraging VR’s anxiolytic properties, it may be possible to decrease the need for intravenous (IV) sedation which is associated with risk of adverse events like apnea and hypoxemia and delayed recovery.

**Objectives:**

This study’s main objective is to determine the impact of VR on IV sedation requirements in adult patients undergoing breast surgery under paravertebral (PV) block without general anesthesia. We will be using Paperplane Therapeutics’ VR headset and software which offer three distinct VR scenario choices. We hypothesize that VR immersion will reduce the need for intraoperative pharmacological sedation. Secondary objectives include assessing the tolerance of patients to the VR headset, examining the impact of the chosen VR scenario on the primary outcome, evaluating the incidence of adverse effects, measuring patient satisfaction, and analyzing the output of the Nociception Level (NOL) Index among awake surgical patients.

**Materials and methods:**

This single center randomized controlled trial will enroll 100 patients aged 18 or above undergoing breast surgery under PV block. Participants will be randomly allocated to the VR group or the control group; both will have access to pharmacological sedation through patient-controlled sedation (PCS). Participants in the VR group will choose between three different VR scenarios and will be allowed to switch between these scenarios during surgery. The primary outcome will be the time-adjusted and weight adjusted dose of self-administered intraoperative propofol. Secondary outcomes will include patient satisfaction, adverse events, and post-anesthesia care unit length of stay (PACU LOS).

**Ethics:**

This trial has been approved by the regional ethics committee (Comité d’Éthique de la Recherche du CIUSSS de l’Est de l’Île de Montréal) on September 9^th^, 2024.

**Trial registration:**

ClinicalTrials.gov (July 25th, 2024). Unique protocol ID: 2025–3802. Trial identification number: NCT06522711.

## 1. Introduction

### 1.1. Background and rationale

Virtual reality (VR) is a novel technology that operates through computer generated three-dimensional environments with which the user can interact. These virtual experiences are accessible on various interfaces, ranging from smartphone screens that display a VR environment to fully immersive headsets and systems that provide haptic feedback, simulating the sense of touch [1]. Over the past decade, the use of VR has expanded across various medical fields. This technology has been used to train residents to perform medical procedures, to allow experienced surgeons to rehearse complex surgeries and has even been used as a substitute for exposure therapy when treating patients with specific phobias or anxiety disorders [2–5].

In anesthesiology, VR immersion has been utilized during various procedures, including orthopedic surgeries of the upper extremities, hip and knee arthroplasties under regional anesthesia, dental care, burn wound treatment, and even during anesthesia induction [6,7]. It has shown significant potential in reducing anxiety and improving patient comfort in these perioperative and periprocedural contexts, although the literature on the topic mostly pertains to pediatric populations [8,9]. Notably, research indicates that interactive, gamified VR scenarios provide significantly greater anxiolysis compared to passive scenarios, likely due to their increased distractibility [10]. While a reduction of procedural anxiety has also been observed in adult populations undergoing VR immersion [11], the assessment of objective outcomes, such as procedural sedative usage, has not been thoroughly explored.

Pharmacological sedation is a crucial part of awake medical procedures, primarily aimed at providing anxiolysis and, when necessary, amnesia. However, these medications can have serious side effects, such as respiratory depression, especially when used alongside opioid analgesics [12]. In fact, research suggests a dose-dependent relationship between the amount of procedural sedatives administered and the length of recovery times in the post-anesthesia care unit (PACU) [13]. This highlights a critical gap in the current literature, as VR could be a low-risk adjunct or alternative to procedural sedation. This is especially relevant for breast surgeries performed only under regional anesthesia, which is increasingly recognized as a valid alternative to general anesthesia. Notably, this approach has been shown to be equivalent to general anesthesia in terms of breast cancer recurrence and persistent incisional breast pain, but often necessitates substantial sedative use, creating an opportunity for VR to potentially reduce sedation requirements [14].

Finally, the Nociception Level (NOL) index is a technology developed by Medasense Biometrics Ltd (Ramat Gan, Israel) [15], which utilizes artificial intelligence algorithms to provide nociception scores ranging from 0 to 100. Using a non-invasive finger probe connected to the PMD-200 monitor, it evaluates photoplethysmography, galvanic skin response, accelerometry, and skin temperature to generate its output. While the NOL index has been validated for use in anesthetized patients undergoing surgery [16], its application in awake surgical populations remains largely unexplored. Investigating its use in this setting is relevant for several reasons. Firstly, awake patients under regional anesthesia with sedation may still experience nociception or discomfort, even if they do not fully verbalize it. Secondly, correlation between NOL trends and patient distress or sedation self-administration could suggest a role for NOL as an early indicator for sedation adjustments. Finally, studying the NOL index in awake patients offers a unique opportunity to compare objective nociception data with real-time subjective patient feedback.

### 1.2. Objectives and hypotheses

The primary objective of this study is to determine if intraoperative virtual reality immersion reduces the use of self-administered propofol for patients undergoing breast surgery under paravertebral (PV) block.

Our secondary objectives are the following

Determine the participants’ initial enthusiasm at the idea of using a VR headset during surgery.Evaluate the level of anxiety and information requirement before the surgery, as they could act as potential confounders if randomization does not adequately balance groups;Evaluate the incidence of adverse effects such as cybersickness, nausea, bradycardia, desaturation, and hypotension;Evaluate the time the patient spent wearing the headset;Evaluate the differences in sedation requirements depending on the type of VR scenario.Evaluate need for additional local anesthesia;Evaluate quantities of fentanyl administered;Evaluate quantities of ketamine administered;Evaluate the requirement of post-operative care and the post-anesthesia monitoring time;Determine the ease of use of the technology, enjoyment of the first scenario chosen and overall satisfaction with the experience.

This trial also has an exploratory objective, which is to investigate the use of the Nociception Level (NOL) index in awake patients undergoing surgery, and the ability to anticipate sedation self-administration via the NOL index.

Regarding our primary objective, we hypothesize that patients undergoing breast surgery under PV block with an immersive VR experience will self-administer less propofol than the control group. We also hypothesize that interactive scenarios will further reduce the requirement for sedation, when compared to non-interactive scenarios.

### 1.3. Trial design

This is the protocol for an open-label, single-center randomized controlled trial.

## 2. Methods

This protocol follows the Standard Protocol Items: Recommendations for Interventional Trials (SPIRIT) Statement guidelines [17].

### 2.1. Participants, interventions, and outcomes

#### 2.1.1. Study setting.

This trial will be conducted at Maisonneuve-Rosemont Hospital, a part of the Centre intégré universitaire de santé et de services sociaux (CIUSSS) de l’est de l’île-de-Montréal (CEMTL), located in Montreal, Quebec, Canada.

#### 2.1.2. Eligibility criteria.

We will recruit consenting adult patients (≥ 18 years) undergoing elective breast surgery under PV block without general anesthesia.

Patients will automatically be excluded from the study if they have any of the following:

Hearing or visual impairment;History of epilepsy, seizure, or severe dizziness;Cognitive or psychiatric impairment that would interfere with informed consent, patient-controlled sedation (PCS) use, or VR engagement, as determined by:A documented clinical diagnosis in the patient’s medical record, orA Montreal Cognitive Assessment (MoCA) test, administered if significant clinical doubt exists;Recent eye or facial surgery or wounds;Inability to use the VR hand controller;Allergy to one of the protocolized drugs.

#### 2.1.3. Interventions.

Prior to entering the operating room, all participants will receive an explanation on the use of intraoperative PCS. For those in the intervention group, a short video will introduce all three VR scenarios, after which participants will select their preferred scenario, which will then be documented.

Upon arrival in the operating room, participants will undergo standard monitoring, including non-invasive blood pressure measurement, pulse-oximetry, and continuous electrocardiography using the Dräger Infinity C700 monitor (Dräger Medical, Lübeck, Germany). Throughout the entire duration of surgery, the NOL index finger probe, which is connected to the PMD-200 monitor (Medasense Biometrics Ltd, Ramat Gan, Israel) will be applied. All intraoperative data and events will be recorded on the research computer.

The attending anesthesiologist will perform PV block before surgery according to their usual practice. Only anesthesiologists with a minimum of 10 PV blocks performed within the last year will be qualified to administer this procedure to trial participants. Standardized doses of intravenous (IV) sedation (0.15 mg/kg of propofol) and IV analgesia (0.5 mcg/kg of fentanyl) will be administered to all participants prior to realization of the PV block and will be repeated if necessary. Once the block is complete, the participant is positioned supine, and the surgeon is ready for disinfection, the VR headset will be applied to those in the intervention group and their chosen scenario will begin. A dedicated research staff member will be present in the operating room throughout the procedure to manage all aspects of the VR intervention, including assisting with headset application, adjusting the VR scenarios upon patient requests, and addressing any technical issues or patient discomfort related to the VR system. Notably, the interactive VR scenarios do not require significant hand or arm movement, as they rely solely on eye-tracking software to aim within the game. The only manual action required is pressing the controller trigger at specific time points. If at any time the patient expresses a desire to discontinue VR during the surgery, we will first offer them an alternate scenario. If they reiterate their willingness to stop, with or without having experienced the new scenario, the headset will be removed for the remainder of the surgery. In case of adverse events attributable to VR gear, such as cybersickness, discontinuation of VR immersion will be at the discretion of the anesthesiologist as well as the patient.

The VR headset to be used is the commercially available Paperplane Therapeutics VR system, specifically designed for medical applications. It offers a fully immersive experience incorporating both visual and auditory elements; notably, it is equipped with integrated near-ear speakers positioned along the side branches of the headset. These speakers are designed to direct sound toward the patient’s ears, providing clear audio at a volume that is perceptible to the patient but remains low enough to avoid disturbing the surgical team or others in the operating room. This design also ensures that patients can continue to communicate freely with clinicians throughout the procedure. A visual representation of the VR device used as well as the possible scenario choices can be seen in Fig 1.

**Fig 1 pone.0327555.g001:**
[figure not shown]
VR headset and scenario choices. A Paperplane Therapeutics VR headset; B Scenario 1 – Calm; C Scenario 2 – Puzzle; D Scenario 3 – Action.

In both groups, the PCS protocol will consist of 0.15 mg/kg boluses of IV propofol with a lockout period of 2 minutes; additional clinician boluses may be administered based on the lead anesthesiologist’s judgment. For breakthrough pain, local anesthesia can be utilized by the surgical team. The anesthesiologist can also administer 0.5 mcg/kg doses of IV fentanyl and, if insufficient, 0.15 mg/kg doses of IV ketamine. If one of the following criteria are met, the anesthesiologist will switch the participant to general anesthesia: inadequate surgical anesthesia despite attempting all previous measures, persistent hemodynamic or respiratory instability (mean arterial pressure < 60 mmHg despite fluid resuscitation and vasopressors or SpO_2_ < 92% that does not respond to non-invasive oxygenation methods) and any surgical complication requiring general anesthesia.

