#### 2.1.4. Outcomes.

The primary outcome is the time-adjusted and weight-adjusted average or median self-administered dose of propofol in mcg/kg/min.

Secondary outcomes include

Initial enthusiasm at the idea of using a VR headset during surgery assessed by research staff on a 10-point Likert scale for all participants, prior to intervention allocation as part of a questionnaire;Level of anxiety and information requirement measured preoperatively by research staff using the Amsterdam Preoperative Anxiety and Information Scale (APAIS) [18];Incidence of intraoperative and postoperative adverse events such as bradycardia (heart rate < 50 bpm), desaturation (SpO_2_ < 92%) and hypotension (MAP < 60) as well as subjective adverse events, such as cybersickness or nausea documented intraoperatively by the anesthesiologist and research staff based on real-time clinical observation or patient self-reporting;Average or median total time, in minutes, during which the VR headset was worn, as well as the percentage of that time relative to the overall duration of the surgery, recorded by dedicated research staff in the operating room using a time log;Average or median total duration in minutes spent by the patient on the VR scenario chosen, and the order in which VR scenarios were presented, recorded by dedicated research staff in the operating room using a time log and a case report form (CRF);Percentage of patients that switched scenarios;Percentage of patients that removed the headset before the end of the surgery;Percentage of patients requiring additional local anesthesia;Weight-adjusted average or median administration of intraoperative IV fentanyl in mcg/kg;Weight-adjusted average or median administration of intraoperative IV ketamine in mg/kg;PACU length of stay (LOS) measured from PACU admission to PACU discharge, based on the PACU nursing records;Ease of use of the technology and enjoyment of the first scenario chosen assessed post-operatively on a 10-point Likert scale in the intervention group only as part of a postoperative questionnaire administered by dedicated research staff;Overall satisfaction with the experience assessed post-operatively on a 10-point Likert scale in both groups as part of a postoperative questionnaire administered by dedicated research staff.Exploratory outcomesNOL index readings over time per patient, recorded continuously intraoperatively via a finger probe, automatically stored and extractable by dedicated research staff from the PMD-200 monitor with precise timepoints. NOL index spikes will be defined;PCS bolus administration timepoints, automatically recorded by the pump device and extracted by dedicated research staff.

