### 2.3. Data collection, management and analysis

#### 2.3.1. Data collection methods.

We will collect data at baseline, intraoperatively and postoperatively to assess primary and secondary outcomes. Participant socio-demographic information, medical history and current medication, will be collected from their medical chart. Their education level and familiarity with VR technology will also be recorded through a preoperative questionnaire. Pre-operative anxiety levels will be assessed using the APAIS, a six-item questionnaire designed to measure both anxiety and the desire for information before surgery. The scale provides an overall anxiety score ranging from 4 to 20 and an information-seeking score ranging from 2 to 10, with higher scores indicating greater preoperative anxiety and a stronger desire for information, respectively. A postoperative questionnaire will be used to collect data on patient satisfaction. It is of note that, aside from the APAIS, both our preoperative and postoperative questionnaires are self-composed and have not yet undergone formal scientific validation.

NOL index data from the PMD-200 medical monitor will be automatically collected by the device. Other intraoperative events, such as propofol self-administration, as well as the use of fentanyl or ketamine, will be manually recorded. Postoperative outcomes will be collected through questionnaires administered to participants prior to their discharge from the PACU, at which point we will also record PACU length of stay (LOS). Adverse events of any kind will be documented when spontaneously reported or observed clinically.

We will monitor and document the number of participants who withdraw from the study. If a participant wishes to discontinue their involvement, they will be removed from the study at their request, and no further data will be collected or retained after their withdrawal.

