### 4.1. Limitations of study design

#### 4.1.1. Unblinded personnel.

Due to the nature of VR interventions, it is difficult for the patient, the anesthesiologist or the surgeon to be blinded to group allocation. We recognize that a sham intervention, such as having a patient wear a non-functional VR headset, could theoretically be considered to achieve blinding. However, we believe this approach presents several important limitations.

Firstly, a non-functional VR headset could potentially induce additional anxiety or feelings of claustrophobia, as it would restrict the participant’s vision without providing the immersive, open 3D environment intended to reduce anxiety; This unintended discomfort could, in turn, bias the results of our trial by exaggerating the perceived benefit of the active VR intervention. Secondly, while a sham headset might initially mask group allocation from personnel, it would not effectively blind participants, who would likely realize they are not receiving an active VR experience. This creates a significant risk that participants could inadvertently reveal their allocation during the procedure, which would hamper the effects of the blinding. Lastly, our trial is designed to compare a VR intervention to the current standard of care; a sham headset does not represent standard practice and would therefore lack clinical relevance in this context.

While our trial will not utilize blinding, the use of PCS minimizes the anesthesiologist’s influence on propofol administration, reducing performance bias.

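### The primary outcome counts only self-administered propofol, no listed outcome captures clinician-given or total propofol, and the statistical methods name the primary outcome differently

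*Protocol article*

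**What the plan says.** The protocol article is consistent on the primary outcome in three places. The abstract says: "The primary outcome will be the time-adjusted and weight adjusted dose of self-administered intraoperative propofol". Section 1.2 sets the primary objective, to "determine if intraoperative virtual reality immersion reduces the use of self-administered propofol". Section 2.1.4 defines the outcome as the "time-adjusted and weight-adjusted average or median self-administered dose of propofol in mcg/kg/min".

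Section 2.1.3 (the text after Fig 1) describes the propofol PCS regimen for both groups, with a "lockout period of 2 minutes; additional clinician boluses may be administered based on the lead" anesthesiologist's judgment. No trigger for these boluses is stated. They stand in the same sentence as the propofol regimen and before fentanyl and ketamine are introduced, so I read them as propofol.

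Section 2.2 says that neither participants nor personnel are blinded after allocation. Section 4.1.1 answers that PCS minimizes the anesthesiologist's "influence on propofol administration, reducing performance bias".

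The secondary outcomes in section 2.1.4 include fentanyl, ketamine and additional local anesthesia. Neither clinician-given nor total intraoperative propofol is listed.

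Two other places use wider terms. The objectives in the abstract ask about IV sedation requirements, and section 2.3.3 describes the primary outcome, in parentheses, as total propofol consumption.

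On recording, section 2.3.1 says that intraoperative events, "such as propofol self-administration, as well as the use of fentanyl or ketamine, will be manually recorded". The exploratory outcomes in section 2.1.4 include "PCS bolus administration timepoints, automatically recorded by the pump device".

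**The concern.** The drug under study reaches the patient by two routes in the operating room, and the listed outcomes count only one of them. The other is controlled by a clinician who knows the allocation. A self-administered dose measures sedation need well only if clinician dosing is similar in the two arms, and nothing in the listed outcomes would let a reader check that.

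The safeguard in section 4.1.1 covers the patient-triggered part only and does not mention discretionary boluses.

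The rationale for the trial (adverse events and slower recovery from sedatives, in the abstract and section 1.1) depends on all the propofol a patient receives. A fall in button presses alone would not establish the benefit that the abstract is about.

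The label in section 2.3.3 makes this worse. Read literally, it includes clinician boluses and is an amount, not a rate per minute. Two analysts could therefore compute two different primary outcomes from the same document, and clinician boluses are part of what separates them.

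**Working it through.** **Inputs from the document.** Sections 2.1.6 and 2.2 give a 30% reduction, a two-sided two-sample t-test at 0.05, 80% power, 90 participants inflated to 100, 1:1 allocation, and a historical median of 525 mg propofol. Section 2.1.3 gives a PCS bolus of 0.15 mg/kg. No SD and no clinician-bolus rate are given.

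**Step 1: the plan's own figure.** Without an SD, 90 cannot be reproduced forward, so I solve backwards.
- At 45 per arm, 80% power needs a standardized difference d = 0.597 (t-test).
- Implied SD = 0.30 / 0.597 = 0.502 of the control mean.
- Check: an SD of 0.50 of the control mean gives a total of 90 (t-test) or 88 (normal approximation).
- 90 / 0.90 = 100, which matches the inflated figure at 10% attrition.
- The implied SD is an assumption. Over SDs of 0.4 to 1.0 of the control mean, the t-test total runs from 58 to 352.

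**Step 2: false benefit when total propofol is equal.** Let s be the share of propofol given by the clinician in the VR arm and c the share in controls. Total propofol is the same in both arms and the SD is unchanged. The apparent difference is s − c of the control mean. The noncentrality is (s − c) / 0.502 × √(45/2), with 88 degrees of freedom. For s = 0.20 and c = 0 this is 0.20 / 0.502 × 4.74 = 1.89.

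| s (VR) | c (control) | Chance of a significant result favouring VR |
|---|---|---|
| 0 | 0 | 2.5% |
| 5% | 0 | 6.8% |
| 10% | 0 | 15% |
| 20% | 0 | 46% |
| 30% | 0 | 80% |
| 10% | 10% | 2.5% |
| 20% | 10% | 15% |

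Only the difference between arms matters.

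**Step 3: the reverse direction.** Suppose VR truly lowers total propofol by 30% and only control patients receive clinician boluses. With 10% of control propofol given by the clinician, the visible difference is 0.90 − 0.70 = 0.20 and power falls from 80% to 46%. With 20%, it is 0.80 − 0.70 = 0.10 and power is 15%.

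**Step 4: how many boluses is a 30% shift?** I assume clinician boluses the size of a PCS bolus (150 mcg/kg), since no size is stated. The answer depends heavily on the assumed dose.
- From an assumed rate R (mcg/kg/min) and duration T (min): 0.30 × R × T / 150. With R = 20 and T = 60 this is 2.4; with R = 40 and T = 90 it is 7.2.
- From the 525 mg median: 0.30 × 525 = 157.5 mg. At an assumed 60 to 80 kg, one bolus is 9 to 12 mg, so 157.5 / 12 = 13 to 157.5 / 9 = 18 boluses.

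The second range is the only one tied to a dose in the document, although that historical dose need not match PCS use. A full 30% artefact may therefore need about 2 to 18 extra clinician boluses per VR patient. Smaller shifts already raise the error rate (Step 2).

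**The case against.** The strongest reply is that self-administered dose is a deliberate and defensible endpoint in an open-label trial. Objective, hypothesis, abstract outcome and outcome definition all agree on it, so it does answer the objective in section 1.2. Making total propofol primary would bring the unblinded anesthesiologist's discretion into the endpoint, which PCS was chosen to limit. That stands, and it is why the primary outcome should stay as it is.

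A reader might infer several stronger things that the document does not support:
- **That clinician boluses will create a false VR effect.** Bias needs dosing that differs by arm, and no rate or direction is given. It could equally hide a true effect.
- **That the safeguard in section 4.1.1 is undone.** The text claims only to minimize influence and reduce bias. It is partial, not void.
- **That headset and controller hinder the PCS button.** All participants are taught PCS (section 2.1.3), VR needs only trigger presses at certain moments without significant arm movement, and patients can speak freely. Nothing says the button is impeded.
- **That manual and pump recording contradict each other.** The pump log is described for bolus timepoints and manual recording for events, so both can be true. Section 2.3.2 adds double data entry for the primary outcome, though this cannot correct a wrong source record.
- **That clinician propofol goes unrecorded.** The list in section 2.3.1 is open-ended, so it may be recorded. The document does not say.

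The label in section 2.3.3 may be loose wording for self-administered dose. If so, it still needs correcting. If not, it conflicts with three other statements of the outcome or objective.

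**Conclusion.** The point holds as a gap in the outcomes and a contradiction in the text. The primary outcome covers self-administered propofol only, discretionary clinician boluses by unblinded staff are allowed, no listed outcome counts them, and section 2.3.3 names a different primary outcome. As written, the plan can support a conclusion about self-administered propofol. It cannot by itself support one about IV sedation requirements if clinician dosing differs by arm.

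The size of any distortion is unknown. The 15%, 46% and 80% figures are illustrations. They rest on 45 per arm, an SD back-solved from the sample size, an SD unaffected by the shift, equal total propofol, and a shift in the VR arm only. With an equal shift the rate stays at 2.5% in that direction.

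**What to change.** 1. Keep self-administered propofol (mcg/kg/min) as the primary outcome and correct section 2.3.3 to match section 2.1.4.
2. Add total intraoperative propofol as a key secondary outcome: PCS plus clinician doses, in mcg/kg/min, over the same time window as the primary, excluding the pre-block doses, and analysed in the same way. State one rule for how propofol given after conversion to general anesthesia is counted, since section 2.3.3 keeps those participants in the intention-to-treat analysis.
3. Report clinician propofol boluses by arm.
4. Limit the conclusion to self-administered propofol unless total propofol points the same way.
5. Name the pump log as the source for PCS doses, with manual entry as backup.

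None of this alters how patients are treated. The cost is one more recorded field, one more analysis and an amendment to the text. The headline claim may become narrower.
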